**Alternative Diagnostic and Treatment Options:**

1. Setting a lower or higher blood flow rate, such as 130 mL/min or 300 mL/min;
2. Using other anticoagulation methods such as heparin or regional citrate anticoagulation.

**VI. Detection Items and Time Points**

1. **Baseline Data:** At the time of patient admission, detailed records will be kept of demographic characteristics, laboratory indicators, examination results, primary disease, comorbidities, concomitant medications, blood pressure, etc.
2. **Filter Lifespan:** Each time a filter is replaced, the usage time of each filter will be recorded. Filters will be replaced based on the following criteria: obvious clotting in the filter, catheter, or venous chamber; filter usage time exceeding 72 hours (even if there are no other issues); patient needs to stop the machine for an outside examination or other treatments; treatment goals are achieved or CRRT is terminated.
3. **CRRT-Related Parameters:** After the CRRT prescription is established, detailed records will be kept of the CRRT prescription, including ultrafiltration rate, access, mode, etc. If the blood flow rate is reduced due to poor circuit performance or the anticoagulation method is adjusted due to coagulation function, the time, adjustment amount, and changes before and after adjustment will be recorded in detail.
4. **Filter Performance and Efficacy:** After CRRT is completed, the filter clearance performance will be recorded, including creatinine clearance, urea nitrogen clearance, cystatin C, and ultrafiltration rate.
5. **Patient Physiological Parameter Changes:** During CRRT, arterial blood pressure will be monitored every 2 hours, and the occurrence of hypotension and other hemodynamic instability events will be recorded.
6. **Adverse Events:** During CRRT, any adverse events that occur will be observed and recorded, including thrombus formation, bleeding complications, etc.
7. **Clinical Outcomes:** After CRRT is stopped, the patient's renal function recovery will be monitored, such as changes in creatinine and glomerular filtration rate. After discharge, the patient's survival status and hospital stay duration will be recorded.

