**III. Research Design, Methods, and Steps**

1. **Research Design**
   - **Study Type:** Single-center, single-blind, prospective randomized controlled trial (RCT)
   - **Randomization Method:** Each patient meeting the inclusion criteria will be randomly assigned to one of three groups (low blood flow rate group, medium blood flow rate group, or high blood flow rate group) by a study coordinator using a computer-generated random number table. Randomization will be conducted in a 1:1:1 ratio to ensure equal numbers of patients in each group, thereby maximizing the balance of patient characteristics and potential confounding factors across the groups. The study coordinator will not be involved in patient treatment or data collection and analysis. Group assignment information will be strictly confidential to ensure fairness. Each patient's randomization information will be recorded in a dedicated study database with appropriate security measures to prevent unauthorized access. All relevant researchers will receive training on the proper handling of randomization information. During patient selection and treatment, only authorized researchers will have access to group assignment information. These authorized personnel, including the principal investigator and the physician assigning treatment, will access the information through an encrypted electronic system to ensure data security and privacy. Unauthorized researchers will not have access to group assignment information to maintain the integrity of the single-blind design. All treatment and patient management decisions will be made by authorized personnel based on group assignment information and clinical conditions.
   - **Research Center:** West China Hospital, Sichuan University

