   - **Sample Size Calculation:** The primary outcome measure of this study is filter lifespan. Therefore, filter consumption quantity is selected for sample size calculation. Based on retrospective and prospective cohort study data from our center, the smallest difference in filter lifespan was observed between the 200 mL/min and 250 mL/min blood flow rate groups. Thus, the maximum possible sample size can be calculated based on the lifespan difference between these two groups. Previous study results showed that the average filter lifespan was 28.09 ± 21.15 hours in the 200 mL/min blood flow rate group and 35.51 ± 17.97 hours in the 250 mL/min blood flow rate group. With a significance level (α) set at 0.05 and power at 0.90, the software PASS (Power Analysis and Sample Size Software) version 15 was used to calculate a sample size of N = 153 per group. Considering a dropout and refusal rate of 5%, the final number of filters required per group is at least 162, totaling at least 486 filters.
2. **Research Methods**

Patients undergoing CRRT at West China Hospital who meet the inclusion and exclusion criteria will be randomly divided into three groups: low blood flow rate group, medium blood flow rate group, and high blood flow rate group. The international standard blood flow rate for anticoagulant-free CRRT is 250 mL/min, while the standard blood flow rate for anticoagulant-free CRRT at our center is 200 mL/min. For hemodynamically unstable patients or those with high circuit pressure, our center reduces the blood flow rate to 150 mL/min based on experience, which is consistent with previous studies defining 150 mL/min as the low blood flow rate group [1]. Therefore, we define 150 mL/min, 200 mL/min, and 250 mL/min as the low, medium, and high blood flow rate groups, respectively.

- **Low Blood Flow Rate Group:** Adjust the CRRT blood flow rate to 150 mL/min.
- **Medium Blood Flow Rate Group:** Adjust the CRRT blood flow rate to 200 mL/min.
- **High Blood Flow Rate Group:** Adjust the CRRT blood flow rate to 250 mL/min.

The remaining CRRT prescription and parameter adjustments will be determined based on the patient's actual condition, experienced clinical physicians, and CRRT specialists. If during CRRT, high blood flow rate causes high vascular access pressure and requires a reduction in blood flow rate, the following principles will be followed:

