- **Stepwise Reduction of Blood Flow Rate:** The blood flow rate will be reduced in increments of 50 mL/min, observing the patient's response and filter performance until a stable state is achieved.
- **Assessment and Recording:** After each adjustment, detailed records will be kept of the blood flow rate before and after adjustment, filter performance, patient's clinical manifestations, and reasons. Clinical judgment will be made based on the patient's actual condition to decide whether further adjustment is needed and to ensure patient safety and treatment efficacy. During data analysis, intention-to-treat analysis and per-protocol analysis will be used separately.
- **Record Filter Lifespan and Adverse Events:** Record the lifespan of the filters in the three groups, as well as the occurrence of clotting events and other negative events related to CRRT such as hypotension.

1. **Research Steps**

[Diagram]

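### Filter life, the primary outcome, can end on an undefined clotting judgement by staff who know the flow rate; restricted database access does not protect it, and the protocol does not say who is blinded

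*Protocol*

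**What the plan says.** Section III of the protocol labels the trial single-blind. Under Randomization Method it describes the protection as control of access to the allocation: "Unauthorized researchers will not have access to group assignment information to maintain the integrity of the single-blind design". The same paragraph lists those who do have access: "These authorized personnel, including the principal investigator and the physician assigning treatment, will access the information through an encrypted electronic system". It then adds: "All treatment and patient management decisions will be made by authorized personnel based on group assignment information and clinical conditions". It does not say which party the blind covers. The only role called blinded anywhere is the statistician for the interim analysis (section IV).

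The arms are blood flow rates of 150, 200 and 250 mL/min. Staff set the rate and may reduce it in steps of 50 mL/min. After each change, "detailed records will be kept of the blood flow rate before and after adjustment, filter performance" (section III, Assessment and Recording). Section VII also has flow rate and filter usage time recorded for each patient.

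On the endpoint, section III states: "The primary outcome measure of this study is filter lifespan". Section VI, item 2, records usage time at each replacement and gives four grounds for replacing a filter:

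- "obvious clotting in the filter, catheter, or venous chamber";
- use beyond 72 hours;
- a stop for an examination or another treatment;
- treatment goals reached or CRRT ended.

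No pressure criterion, grading scale, masked assessor or adjudication goes with the first ground.

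**The concern.** Limiting who can open the allocation database protects the allocation record. It cannot hide a setting that the treating team enters and charts. The people who judge whether a circuit has clotted therefore know the arm, and that judgement fixes the end of the primary outcome time. If they act sooner on the same clot in one arm than in another, recorded filter life will differ between arms even when clotting does not.

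Two features raise the stakes. Section I states an expectation that staff may share, namely that faster flow lowers the risk of clotting. Section IV allows the study to stop early if the interim comparison of filter lifespan gives P < 0.05 and the difference is considered sufficient to prove the primary hypothesis, so a spurious difference could also end the trial.

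**Working it through.** **Who knows the arm, and who ends the outcome time**

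1. Outcome: filter lifespan (section III). It ends at replacement (section VI, item 2).
2. Of the four grounds for replacement, only the 72-hour limit is free of judgement. Clotting is judged. The stops for examinations, other treatment or treatment goals are also decided by staff.
3. Those decisions are made by people who hold the allocation (section III, Randomization Method). The flow rate is in any case set and charted at the bedside (section III, Research Methods; section VII). That bedside staff know the arm is an inference, but a firm one.
4. The interim statistician, though masked, works on times already fixed. The coordinator's separation from treatment and data collection protects allocation, not the clotting call.

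**The planning figure**

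Inputs from section III: 28.09 (SD 21.15) h at 200 mL/min, 35.51 (SD 17.97) h at 250 mL/min, α 0.05, power 0.90, dropout 5%.

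- Difference: 35.51 − 28.09 = 7.42 h.
- Common SD: √((21.15² + 17.97²)/2) = 19.62 h.
- Normal approximation, two-sided: n = 2 × (1.960 + 1.282)² × 19.62² / 7.42² = 147 per group. The exact t-test gives 148. Multiplying by π/3 for a Mann-Whitney test gives 155.
- The plan's 153 lies between these, and its t-test power is 0.909. 153/0.95 rounds up to 162, and 3 × 162 = 486.

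The sample size is not in dispute; 7.42 h serves here only as the yardstick.

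**How much a differential would matter**

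The documents give no figure for a shift in recorded life between two arms, so 1, 2 and 3 h are assumptions.

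- Share of the planned effect = shift / 7.42.
- If only half of the filters shift (also an assumption), the share is 0.5 × shift / 7.42.
- Last two columns: two-sided t-test, 153 per arm, SD 19.62 h, shift averaged over all filters. Standard error = 19.62 × √(2/153) = 2.24 h. The smallest significant difference is about 4.4 h.

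| Assumed shift | Share, all filters shift | Share, half shift | False-positive rate, no true difference | Power if the shift opposes a true 7.42 h |
|---|---|---|---|---|
| 0 h | 0% | 0% | 0.05 | 0.91 |
| 1 h | 13% | 7% | 0.07 | 0.81 |
| 2 h | 27% | 13% | 0.14 | 0.67 |
| 3 h | 40% | 20% | 0.27 | 0.50 |

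The last two columns are indicative only. Section XI plans Kaplan-Meier and Cox analyses, for which a shift in the mean does not translate directly, and the calculation treats filters as independent.

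**The case against.** The strongest reply is that a pump setting cannot be masked from the people operating it, and that the protocol does not pretend otherwise: section III says openly that treatment decisions use the allocation. That stands. A reader might infer that the protocol falsely claims bedside staff are blinded. It does not; it leaves the blinded party unnamed. Nor does any passage support the inference that the patient and the final analyst are blinded, so that wording cannot simply be inserted.

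A reader might also infer that the bias must favour high flow. Section I points that way, but the objective in section II is to find the best rate, 200 mL/min is the centre's own standard, and the first reference is a randomised trial whose title reports no improvement in circuit life with faster flow. The direction is open.

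The size is open too. The 72-hour limit is immune to a clotting judgement, so a shift would not touch every filter. It would also go too far to say that bias could never be detected afterwards. Sections III, VI and VII call for records of clotting events, filter performance, blockages and timed flow changes, and section IX refers to operating procedures that are not shown.

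Lastly, an obvious remedy has its own fault. Section III itself links high flow to high access pressure. One absolute pressure limit as the sole primary event could therefore be reached sooner at high flow for reasons other than clotting. Filters changed on judgement before that limit would be censored informatively. This objection stands and shapes the fix.

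None of this answers the central point. When the team cannot be masked, an objective event definition is the main protection left, and the protocol has none for clotting.

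**Conclusion.** The point holds as a weakness of design. Following the protocol as written leaves the clotting end of the primary outcome to the judgement of staff who know the arm, with no objective check, while the stated safeguard acts elsewhere. The documents support the possibility of differential ascertainment. They do not show that it will occur, which arm it would favour or how large it would be. On the assumption of an average 1 to 3 h differential over all filters, it would amount to 13% to 40% of the planned 7.42 h; if half of the filters were affected, 7% to 20%.

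This is not a matter for an unseen analysis plan. The blinding statement and the replacement grounds are set in the protocol, and an analysis plan cannot recover evidence that was not captured when the filter was changed. The correction should be made, but nothing here shows that the trial's result would be invalid.

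**What to change.** Before the first patient:

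- **Blinding statement (section III).** State that bedside staff know the arm, and have the sponsor confirm who, if anyone, is blinded.
- **Event definition for analysis (section VI, item 2).** Add an objective definition of clotting that does not depend on the arm, for example a change from each circuit's own baseline pressure at the prevailing flow, or a machine stop. Do not use one absolute pressure limit for all arms.
- **Times and reasons.** Take filter start and end times from the machine log where available, and code the reason for every filter end.
- **Analysis (section XI).** Keep all clotting-coded filter ends as events in the primary analysis. Add a prespecified sensitivity analysis restricted to objectively confirmed clotting, and note that filters changed before confirmation may be informatively censored in it.

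The definition serves the analysis only. When a filter is changed remains a clinical decision.

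The cost is some rewording, some data extraction and one more analysis. That the machines store retrievable pressures and times is an assumption; the documents do not say so.

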**I. Research Background**

Continuous renal replacement therapy (CRRT) is an effective treatment for acute kidney injury (AKI). Due to its continuous nature, mildness, and minimal impact on hemodynamics, it has been widely applied in clinical practice. The efficacy of CRRT is not only related to the treatment modality but also closely associated with the lifespan of the filter. A longer filter lifespan means fewer replacements and a lower risk of complications, thereby enhancing the safety and cost-effectiveness of the treatment.

Anticoagulation is a conventional practice in CRRT to prevent filter clotting and prolong filter lifespan. However, the use of anticoagulants carries a risk of bleeding, especially in patients with a tendency to bleed. Therefore, anticoagulant-free strategies have gained increasing attention, aiming to reduce anticoagulant-related complications while maintaining filter function and lifespan.

Blood flow rate is a critical operational parameter in CRRT, influencing both filter clotting risk and treatment efficacy. A higher blood flow rate can reduce the dwell time of blood in the filter, thereby lowering the risk of filter clotting and thrombus formation. However, for hemodynamically unstable patients, a higher flow rate may lead to decreased blood pressure and reduced cardiac output. An appropriate blood flow rate can ensure effective filtration and clearance of metabolic waste, thereby improving renal function. Thus, studying the impact of blood flow rate on filter lifespan in anticoagulant-free CRRT is of significant importance for optimizing treatment protocols, reducing medical resource consumption, and improving patient outcomes.

This study aims to investigate the impact of different blood flow rate settings on filter lifespan in anticoagulant-free CRRT, in order to provide more precise treatment parameters for clinical practice and improve the therapeutic outcomes for AKI patients.

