**II. Research Objectives**

1. **Primary Objective:** To evaluate the impact of different extracorporeal blood flow rates on filter lifespan in CRRT without anticoagulation. By comparing filter lifespans under different blood flow rates, the optimal extracorporeal blood flow rate will be determined to maximize filter lifespan, reduce the number of filter replacements during CRRT, lower treatment costs, and improve patient outcomes.
2. **Secondary Objectives:**
   1. To explore the performance and efficacy of CRRT filters under different blood flow rates, including creatinine clearance, urea nitrogen clearance, and ultrafiltration rate.
   2. To analyze changes in hemodynamic parameters and physiological indices of patients under different blood flow rates, including arterial blood pressure, to assess the impact on patient physiological status.
   3. To study the impact of different blood flow rates on adverse events during CRRT, such as thrombus formation and bleeding complications, to evaluate safety and feasibility.
   4. To assess the clinical outcomes of CRRT treatment under different blood flow rates, including renal function recovery, survival rate, and hospital stay duration, to determine the optimal treatment strategy.

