**IV. Case Selection**

1. **Inclusion Criteria**
   1. Patients undergoing CRRT;
   2. Age 18 years or older;
   3. No anticoagulant used during CRRT;
   4. Informed consent provided by the patient or their legal guardian/agent.
2. **Exclusion Criteria**
   1. Patients with severe coagulation disorders or undergoing anticoagulant therapy;
   2. Patients receiving intermittent renal replacement therapy (IRRT) or other non-CRRT treatments;
   3. Pregnant women.
3. **Criteria for Study Termination**
   1. **Safety Issues:** Serious adverse events: If during the study, the incidence of serious adverse events related to treatment such as hypotension, malignant arrhythmias, or death is significantly higher in one group compared to the other two groups, or exceeds the predefined safety threshold, consideration should be given to terminating that group's study. The safety threshold is set based on data from similar previous studies and the opinions of clinical experts to ensure patient safety. For example, if the incidence of bleeding events exceeds 10% and is 5% or more higher than the other groups; the incidence of thrombotic events exceeds 5% and is 3% or more higher than the other two groups; the incidence of infectious events exceeds 15% and is 5% or more higher than the other groups; the incidence of cardiovascular events exceeds 8% and is 4% or more higher than the other two groups [2,3].
   2. **Inadequate Effectiveness:** Interim analysis: Interim analysis will be conducted after 50% of the patients have been enrolled, performed by an independent statistician who is blinded to treatment allocation.
   3. **Interim Analysis Objectives:** To assess filter lifespan in different blood flow rate groups, compare filter blockage rates among groups, and evaluate the incidence of adverse events.
   4. **Interim Analysis Indicators:** Primary outcome measure: Filter lifespan (hours); Secondary outcome measures: Filter clotting rate, incidence of adverse events (bleeding, thrombus formation, etc.).
   5. **Interim Analysis Method:** Kaplan-Meier survival analysis will be used to assess filter lifespan, and the Log-rank test will be used to compare differences in filter lifespan among different groups. The chi-square test will be used to compare differences in filter blockage rates and adverse event incidence among groups.

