**XI. Statistical Analysis**

SPSS software (version 27.0, SPSS Inc., USA) and R version 4.2 (R Foundation for Statistical Computing, Vienna, Austria) will be used for data analysis.

1. **Descriptive Statistical Analysis:** Basic characteristics of the study sample will be described, including demographic features, laboratory indicators, underlying diseases, etc. Descriptive statistical analysis will also be conducted on filter lifespan, filter performance indicators, and changes in patient physiological parameters across different blood flow rate groups, including mean values, standard deviations, medians, etc.
2. **Survival Analysis:** Survival analysis methods (e.g., Kaplan-Meier curves) will be used to compare differences in filter lifespan among different blood flow rate groups. Cox proportional hazards models will be employed to analyze factors that may affect filter lifespan, such as blood flow rate, patient age, underlying diseases, etc.
3. **Analysis of Variance (ANOVA):** Differences in filter performance indicators among different blood flow rate groups will be analyzed using ANOVA.
4. **Safety and Adverse Event Analysis:** The incidence of adverse events (e.g., thrombus formation, bleeding complications) among different blood flow rate groups will be compared using chi-square tests or Fisher's exact tests to assess the safety of CRRT treatment at different blood flow rates.
5. **Clinical Outcome Analysis:** Appropriate statistical methods will be used to compare clinical outcomes, such as renal function recovery, survival rate, and hospital stay duration, among different blood flow rate groups.

A P-value of less than 0.05 will be considered statistically significant.

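### Renal recovery is measured by creatinine and GFR change after CRRT, and hospital stay as plain duration; neither accounts for death, and creatinine can also reflect circuit or later dialysis removal

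*Protocol*

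**What the plan says.** Secondary objective 4 (Protocol Section II) is: "To assess the clinical outcomes of CRRT treatment under different blood flow rates, including renal function recovery, survival rate, and hospital stay duration". The stated purpose is to choose the best treatment strategy.

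Section VI item 7 is the only operational description of these outcomes. On recovery: "After CRRT is stopped, the patient's renal function recovery will be monitored, such as changes in creatinine and glomerular filtration rate". On the other two: "After discharge, the patient's survival status and hospital stay duration will be recorded". Item 7 gives no reference value, threshold or time point, and no condition that the patient be free of dialysis. It does not say which stop of CRRT counts, although Section VIII allows for several courses per patient. Renal replacement status after CRRT is not among the items listed in Section VI.

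Section XI item 5 leaves the analysis open: "Appropriate statistical methods will be used to compare clinical outcomes, such as renal function recovery, survival rate, and hospital stay duration".

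On population, Section I states the aim as to "improve the therapeutic outcomes for AKI patients". The first inclusion criterion in Section IV is only "Patients undergoing CRRT". The second exclusion criterion is "Patients receiving intermittent renal replacement therapy (IRRT) or other non-CRRT treatments". Chronic or end-stage kidney disease is not excluded by name.

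**The concern.** The difficulty lies in the measures the protocol names, not only in detail it leaves out. Three features matter for the comparison between arms.

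- **Creatinine is not a clean marker of the kidney here.** While the circuit runs, it removes creatinine. A value taken soon after the stop still carries that removal, and a later value carries any further dialysis. GFR estimated from creatinine inherits the problem. Secondary objective 1 explores whether creatinine clearance differs by blood flow rate, so the intervention might move the marker without any change in the kidney.
- **Death removes the recovery value.** A patient who dies on CRRT has no creatinine after CRRT.
- **Death shortens stay.** As plain duration, an early in-hospital death counts as a short stay, which reads as benefit.

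A smaller matter is that patients already on maintenance dialysis cannot recover kidney function in the sense intended, and the entry criteria do not clearly keep them out.

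What is at stake is a misleading statement on two of the three outcomes meant to guide the choice of flow rate.

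**Working it through.** The protocol gives no rate, mean or power for renal recovery, survival or stay, so there is no stated figure to reproduce. The inputs in steps 2 to 4 are assumptions chosen to show direction and scale.

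**1. What the recovery measure contains.** The measure is a creatinine (or GFR) value after CRRT minus an unnamed reference. The value after CRRT depends on native kidney function, on what the circuit removed before the stop, and on any dialysis after it. Only the first is recovery. With no time point and no dialysis-free condition, nothing in item 7 separates the three. The direction of any bias by arm is unknown, because Section III leaves the rest of the CRRT prescription to clinicians.

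**2. Recovery when deaths have no value.** Let r be the share of all randomised patients who recover alive, and m the mortality. Among patients with a value, the recovery rate is r / (1 − m). Take r = 0.30 in both arms, so there is no true difference.

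| Mortality, arm A vs arm B | Apparent recovery, A | Apparent recovery, B |
|---|---|---|
| 50% vs 50% | 0.30/0.50 = 60% | 60% |
| 50% vs 55% | 60% | 0.30/0.45 = 67% |
| 50% vs 60% | 60% | 0.30/0.40 = 75% |

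The arm with more deaths looks better. With equal mortality there is no distortion. If deaths count as no recovery, every row reads 30% versus 30%. The table treats all deaths as occurring before a value is obtained, which is the extreme case.

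**3. Hospital stay as plain duration.** Assume deaths at about day 10 and survivors staying about 30 days. Mean stay = 10m + 30(1 − m) = 30 − 20m. At m = 0.50 this is 20 days and at m = 0.60 it is 18 days, so ten more points of mortality appear as 2.0 days saved.

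For days alive and out of hospital to a fixed day T later than 30, the in-hospital deaths score 0 and survivors score T − 30. The mean is (T − 30)(1 − m), which falls as mortality rises, so the sign is now right. T must lie beyond most discharges, or nearly every patient scores 0.

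**4. Patients who cannot recover.** If a share q of each arm cannot recover, a true difference among the rest is multiplied by (1 − q). Ten points become 10 × 0.9 = 9 at q = 10% and 10 × 0.7 = 7 at q = 30%. Randomisation should balance q across arms, so this is dilution and favours no arm.

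For scale, with 162 patients per arm and recovery of 50% versus 65% in those able to recover, power is 78%. It falls to 68% at q = 10% and 49% at q = 30%. The 162 is itself uncertain for this purpose: Section III counts filters, while the abstract calls the total of 486 cases.

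**The case against.** The strongest reply is that this is one part of the last of four secondary objectives, that handling of deaths is commonly left to a statistical analysis plan, and that such a plan may exist. Several parts of that reply stand.

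- A reader might infer that secondary objective 4 cannot be answered at all. The documents do not support that. Survival is one of its three outcomes, does not depend on creatinine, and can be compared as it is.
- A reader might infer that death is ignored. It is not: survival status is recorded and compared. What is missing is a link from death to recovery and stay.
- A reader might infer that recovery will be analysed in survivors only. No section says so. It is the likely result of the data item 7 calls for, not a stated analysis set.
- Objective 1 only explores clearance by flow rate and predicts no difference. Item 7 speaks of monitoring and gives examples, so a later creatinine value in a patient off dialysis would carry little of the circuit's effect.
- The second exclusion criterion may remove some maintenance-dialysis patients, depending on whether it means current or usual treatment.

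The reply does not dispose of the point. Eligibility, the outcome measure and the data collected belong in a protocol. Since dialysis status after CRRT is not a listed item, a later analysis plan could find that the data needed to repair the measure were not collected. Reading stay beside mortality helps the reader, but leaves a plain mean that moves the wrong way.

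**Conclusion.** The concern holds for two outcomes, renal recovery and hospital stay. As the protocol describes them, an arm with more deaths could look better on both, and an arm with more creatinine removal could look better on recovery. Survival is unaffected, and so are the filter-lifespan primary outcome and its sample size.

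The size cannot be taken from the documents. On the assumptions above, a null recovery comparison could read 60% versus 75% when mortality differs by ten points, and mean stay could be shortened by 2.0 days. Both distortions vanish if mortality is equal across arms. The mismatch between the AKI aim and the entry criteria is visible in the text, but its effect is mainly dilution, to an unknown extent. This is a cheap improvement to make to a secondary objective and gives no reason to doubt the main comparison.

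**What to change.** In Protocol Section VI item 7:

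- Define renal recovery as alive and free of renal replacement therapy at hospital discharge, or on one fixed day, with deaths counted as no recovery. Keep creatinine and GFR change as descriptive only.
- Analyse recovery in patients not on maintenance dialysis before admission, identified from the baseline record of primary disease and comorbidity. Because this set is defined before treatment, the randomised comparison within it is preserved. State how this set relates to the AKI aim in Section I, and clarify what the second exclusion criterion means for maintenance dialysis.
- Report hospital stay in a death-aware form, such as days alive and out of hospital to a fixed day later than most discharges, beside mortality.

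Cost: renal replacement status must be added as a collected item, with one status check per patient discharged earlier if a fixed day is used. The recovery analysis set becomes slightly smaller. Randomisation, treatment and the primary outcome do not change.
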